### Statistical considerations

#### Sample size estimation

Among 3.3 million people treated for diabetes mellitus in France, at least 3 million are estimated to have T2DM. Based on previous data, about 2.4 million T2DM individuals would be free of a history of CAD, 38% would have at least two cardiovascular risk factors, and a history of microvascular or macrovascular disease would be present in more than 10% of patients [24, 25]. Hence, we estimated that at least 90,000 patients would be eligible for our study.

### Statistical analysis plan

The data will be analysed by the biostatistician of the “Clinical Epidemiology Unit” of the University Hospital of Bordeaux (USMR). Analyses will be performed using SAS® software, version 9.4 or later (SAS Institute, Cary, NC, USA, http://www.sas.com) and all tests will be performed at the first-order error risk α = 5%. The flow-chart (CONSORT), as well as the characteristics of patients at inclusion (eligibility criteria, epidemiological, clinical, biological characteristics and treatment use) will be presented. Confounding factors will be taken into account through a hdPS score that will involve around 500 variables, according to the Bross formula [26]. A principal component analysis will then allow us to reduce the dimensionality to 30 components, and the goodness of fit of this hdPS score will be estimated by a graphical comparison of the score distribution and by standardized mean differences between the two study groups [27]. Comparisons between the two groups will be carried out with and without adjustment for the hdPS score, and the hypotheses of the different regression models chosen, will be systematically verified.

Regarding the analysis of the primary endpoint, a gross estimate of the incremental cost per life-year gained at 5 years will be conducted. The confidence interval (CI) of this incremental cost-effectiveness ratio will be estimated by boostrap (5000 iterations). The analysis will be performed as Intent to Treat. To investigate a possible relationship between the frequency of screening and survival, we will define four different subgroups: screening conducted at least once a year, less than once a year (and at least once every two years), less than once every two years (and at least once every three years), and only once during the follow-up period.

A cost-consequence analysis will be performed linking results of all direct costs (observed during the following period) and results on major cardiovascular events. A budget impact analysis will be conducted to determine the public expenses of the spread of a systematic screening for silent ischemic CAD.

Cardiovascular events will be expressed as numbers, cumulative incidence and incidence rates. Kaplan–Meier curves will be elaborated to plot the incidence of endpoints according to study groups (CAD screening versus no screening). Unadjusted comparisons between groups will be done using a log-rank test. Cox proportional hazards regression models will be computed to estimate Hazard ratios, with related 95% CIs, after adjustment for hdPS score.

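### Compressing about 500 Bross-selected variables to 30 principal components ignores exposure and outcome, is not required by the sample size, and can leave substantial measured confounding in the adjusted results

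*Protocol article*

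**What the plan says.** The protocol article's Statistical analysis plan section describes confounding control in two steps. The first: "Confounding factors will be taken into account through a hdPS score that will involve around 500 variables, according to the Bross formula". The second: "A principal component analysis will then allow us to reduce the dimensionality to 30 components". The section gives no reason for compressing and no criterion behind the number 30.

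The score is to be assessed "by a graphical comparison of the score distribution and by standardized mean differences between the two study groups". The section sets no threshold and no consequence, and does not say whether the differences are taken on the original variables, the components or the score. Group comparisons are planned with and without the score, and for the clinical endpoints "Cox proportional hazards regression models will be computed to estimate Hazard ratios, with related 95% CIs, after adjustment for hdPS score".

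On size, the Sample size estimation section states that "we estimated that at least 90,000 patients would be eligible for our study". The Strengths and limitations section relies on this method for confounders that can be measured and for those that cannot.

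**The concern.** The Bross formula ranks a variable by the bias it could cause, using its association with exposure and with outcome. Principal component analysis uses neither. It keeps the directions in which the covariates vary most together. A strong confounder that is only weakly correlated with the other variables contributes little to the first 30 components, so the score hardly adjusts for it. The plan therefore selects for confounding potential and then reduces by a criterion unrelated to it.

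The comparison is not randomised, and this score is the only stated adjustment for confounding. If the score drops part of the measured confounding, results reported as adjusted carry the remainder. In a cohort of this size, even a modest spurious hazard ratio could look statistically significant.

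**Working it through.** **1. The plan's sample size.** The Sample size estimation section gives 2.4 million people with type 2 diabetes and no coronary disease, 38% with at least two risk factors, and more than 10% with micro- or macrovascular disease. 2,400,000 × 0.38 × 0.10 = 91,200, which agrees with the stated minimum of 90,000.

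**2. Does that size require compression?** The share screened is not stated, so the smaller group's share is an assumption, taken from 5% to 50%. Patients per parameter in the smaller group = 90,000 × share ÷ number of parameters.

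| Smaller group | Patients | Per variable (500) | Per component (30) |
|---|---|---|---|
| 50% | 45,000 | 90 | 1,500 |
| 30% | 27,000 | 54 | 900 |
| 20% | 18,000 | 36 | 600 |
| 10% | 9,000 | 18 | 300 |
| 5% | 4,500 | 9 | 150 |

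Ten per variable needs 10 × 500 = 5,000 patients, and 5,000 ÷ 90,000 = 5.6%. Above about 6%, sample size does not call for compression.

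**3. How much confounding can be lost?** The documents do not give the correlation among the covariates, so this was simulated over a range, always with a true effect of zero.

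*Simulation A.* 500 binary covariates (prevalence 1% to 50%), 100 of them individually chosen as confounders, 30% screened, 40,000 patients, continuous outcome, overlap weighting, one run per scenario. Covariates were driven by 10, 30 or 100 latent factors at five loadings (15 scenarios). Share of crude bias left by the 30-component score:

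| Loading | Share left |
|---|---|
| 0 | 88% to 99% |
| 0.3 | 54% to 79% |
| 0.5 | 31% to 77% |
| 0.7 | 16% to 67% |
| 0.85 | 10% to 62% |

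In 13 of 15 scenarios 30% or more remained. The exceptions (16% and 10%) had strong correlation driven by only 10 factors. The components explained 7% to 48% of covariate variance. With all 500 variables the remaining bias lay between −0.020 and +0.020 (Monte Carlo standard error about 0.013), against crude biases of 0.100 to 0.869.

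*Simulation B.* The same 15 scenarios with a survival outcome and the score as a covariate in a Cox model, which is closer to the plan; true hazard ratio 1.00, two runs each. Crude hazard ratios were 1.19 to 1.90; adjusted for the 30-component score, 1.09 to 1.20; adjusted for the 500-variable score, 0.99 to 1.02. The 30-component score left 13% to 95% of the log-scale bias, and again 30% or more in 13 of 15 scenarios.

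*Simulations C and D.* These varied how confounding arises. C used overlap weights, 20,000 patients, and 10 or 30 factors at loadings 0.5 and 0.7. D adjusted for the score as a covariate. Share of crude bias left:

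| Source of confounding | 30 components | 500 variables |
|---|---|---|
| C: 60 individual covariates | 27% to 59% | −2% to 7% |
| C: all 500, equal and same direction | within ±4% | within ±4% |
| C: shared latent factors only | 15% to 34% | 15% to 34% |
| D: individual covariates | 22% to 94% | about 0% to 4% |
| D: all 500, mixed signs | 67% to 95% | about 0% to 4% |
| D: shared latent factors only | 12% to 33% | 11% to 33% |

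**4. Would the balance check show it?** In Simulation A, 2 to 16 of the 100 confounders kept a standardized difference above 0.1 with the 30-component score, and none did with all 500 variables. In Simulation B's settings, 0 to about 5 of the 500 covariates exceeded 0.1. With overlap weighting on the 30-component score, the difference on the score itself was 0.000. A check on the original variables can therefore reveal the loss, though not in every scenario. A check on the score alone did not.

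**The case against.** The strongest objection is that the size of the loss depends on a data structure nobody has shown. Where confounding acts through a few shared dimensions such as disease severity or use of care, 30 components capture it as well as 500 variables do. Where all variables confound equally in one direction, neither score leaves material bias. This stands, and it is why the point can only be conditional. It does not rescue the choice: in these simulations the 500-variable score was never materially worse, and in the other structures it was much better.

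Sample size is also not the only reason to compress. Collinearity and extreme scores are others. That is fair, but a penalty and trimming deal with both without discarding the ranking.

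The article is condensed, so the reasoning, or a statement that differences are computed on the original variables, may sit in the full plan. The point does not rest on those gaps. The reduction to 30 components is a stated commitment.

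A reader might infer three stronger things that the documents do not support:

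- **That adjusted hazard ratios will stay close to the crude ones.** This holds only under weak correlation. Under strong correlation with few factors, most of the bias was removed.
- **That the planned balance check will miss the problem.** It may reveal it if done on the original variables; the text does not say.
- **That the full score would remove confounding.** With latent-factor confounding it left 11% to 34% as well.

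**Conclusion.** The point holds in conditional form. The plan commits to an unexplained compression that ignores exposure and outcome, at a sample size that does not require it, and this can leave substantial measured confounding in the adjusted results. Where confounding ran through individual covariates, about 10% to nearly 100% of the crude bias remained. Where it ran only through shared latent factors, there was no meaningful difference from the uncompressed score.

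The sample-size argument assumes that the smaller group is at least about 6% of 90,000. The bias figures rest on simulated covariates, few runs per scenario and smaller cohorts than planned. They show direction and range and do not estimate this study's bias. The change is worth making before analysis because it costs little and did not perform materially worse in any structure tried.

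**What to change.** Make the primary propensity score the one fitted on the roughly 500 Bross-selected variables themselves. Use a ridge or lasso penalty if separation or collinearity occurs, and trim extreme scores if needed. Report standardized mean differences after adjustment on every original variable. Keep the 30-component score as a sensitivity analysis, so that agreement or divergence between the two can be seen.

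The cost is a few lines in the analysis plan, more computing time and somewhat more variable scores. No new data are needed.

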**Methods:**

SCADIAB is a comparative nationwide cohort study using data from the French National Health Data System. The main inclusion criteria are: age ≥ 40 years, DT2 diagnosed for ≥ 7 years, with ≥ 2 additional cardiovascular risk factors plus a history of microvascular or macrovascular disease, except CAD. We estimated ≥ 90,000 eligible participants for our study. Data will be extracted from 01/01/2008 to 31/12/2019. Eligible participants will be identified during a first 7-year selection period (2008–2015). Each participant will be assigned either in experimental (CAD screening procedure during the selection period) or control group (no CAD screening) on 01/01/2015, and followed for 5 years. The primary endpoint is the incremental cost per life year saved over 5 years in CAD screening group *versus* no CAD screening. The main secondary endpoints are: total 5-year direct costs of each strategy; incidence of major cardiovascular (acute coronary syndrome, hospitalization for heart failure, coronary revascularization or all-cause death), cerebrovascular (hospitalization for transient ischemic attack, stroke, or carotid revascularization) and lower-limb events (peripheral artery disease, ischemic diabetic foot, lower-limb revascularization or amputation); and the budget impact for the French Insurance system to promote the cost-effective strategy. Analyses will be adjusted for a high-dimension propensity score taking into account known and unknown confounders. SCADIAB has been funded by the French Ministry of Health and the protocol has been approved by the French ethic authorities. Data management and analyses will start in the second half of 2021.

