### Study endpoints

#### Primary endpoint

The incremental cost per life year saved over 5 years in CAD screening group *versus* no CAD screening.

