### Strengths and limitations

The key strength of our study is the collection of a comprehensive range of clinical features, cardiovascular procedures, history of pharmacological therapies or surgery, major events and survival status in the whole French population of patients with T2DM and a very high cardiovascular risk during an overall period of 12 years. SCADIAB findings will have a broader generalizability for all T2DM patients at a very high cardiovascular risk. Our study will provide a line of complementary evidence (further to RCTs’ findings) in terms of routine CAD screening in a contemporary cohort of patients with T2DM in real-world settings. SCADIAB will be more economical and time efficient than RCT, but a number of intrinsic limitations need to be acknowledged. The retrospective and non-randomized design of our study is subject to bias (selection, information, detection) and confounding factors. To limit selection bias, our study population will be rigorously defined using pre-specified inclusion criteria (T2DM for at least 7 years, with at least 2 cardiovascular risk factors and one or more organ damage) extracted from reliable and valid SNDS database. The 7-year selection period leading to assignment of each individual to one of the two study arms (CAD screening or absence of CAD screening) will limit information bias. We will use validated algorithms to identify inclusion criteria and endpoints [29–31]. Also, the cardiovascular investigation required for study arms assignment (stress test, scintigraphy, stress echocardiography…) will be recorded exhaustively in the SNDS database. We believe that the detection bias will be limited in our study as we have access to the SNDS database covering the whole French population including death registry. Finally, we will use the hdPS method to control measurable confounding factors as well as unknown or unmeasurable ones [32–34].

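### The primary ICER is specified only as a gross estimate, although the plan relies on hdPS adjustment elsewhere, and it is not stated which estimate is primary

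*Protocol article*

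**What the plan says.** The primary endpoint is defined as "The incremental cost per life year saved over 5 years in CAD screening group" against no screening (Primary endpoint).

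The Statistical analysis plan section gives one sentence on how it will be estimated: "a gross estimate of the incremental cost per life-year gained at 5 years will be conducted". The next sentence says that the confidence interval "of this incremental cost-effectiveness ratio will be estimated by boostrap (5000 iterations"). Gross is not defined, and no adjusted ICER, adjusted cost difference or adjusted life-year difference is named.

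Other parts of the article speak of adjustment in general terms:

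- Abstract, Methods: "Analyses will be adjusted for a high-dimension propensity score taking into account known and unknown confounders", with no exception for the primary endpoint.
- Statistical analysis plan, just before the primary-endpoint paragraph: "Confounding factors will be taken into account through a hdPS score that will involve around 500 variables", and then "Comparisons between the two groups will be carried out with and without adjustment for the hdPS score".
- Statistical analysis plan, on the clinical events: "Cox proportional hazards regression models will be computed to estimate Hazard ratios, with related 95% CIs, after adjustment for hdPS score".
- Strengths and limitations: "The retrospective and non-randomized design of our study is subject to bias (selection, information, detection) and confounding factors". The same paragraph names the hdPS as the means of controlling confounding.

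**The concern.** Patients fall into the two groups according to whether a physician ordered a test during the selection period. The reasons for ordering or withholding a test may also bear on survival and cost, so a crude ICER does not estimate the effect of screening. In a section that contrasts comparisons with and without adjustment, gross most naturally means unadjusted. That is the only version of the primary ratio the article fixes, and the only one given an interval.

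The clinical events, which are secondary, have a named adjusted model; the primary endpoint has none. With about 90,000 patients the bootstrap interval could be narrow around a biased value. The Conclusions section says the findings are meant to inform payers and future recommendations, so the choice of headline ratio matters. If the article leaves it open, it can be settled after both versions have been seen.

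**Working it through.** **The plan's own figure.** From Sample size estimation: 2,400,000 people with type 2 diabetes and no CAD × 0.38 with at least two risk factors × 0.10 with vascular disease = 91,200. This agrees with the stated minimum of 90,000. It is a count of eligible patients, so it sets the precision below but does not decide the point.

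**What the text fixes.**

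| Place | Adjustment stated | Names the ICER? |
|---|---|---|
| Abstract, Methods | hdPS, all analyses | Not singled out |
| Statistical analysis plan, general rule | With and without hdPS | Not singled out |
| Statistical analysis plan, primary endpoint | Gross, bootstrap CI on that ratio | Yes |
| Statistical analysis plan, Cox models | hdPS | No, clinical events |
| Strengths and limitations | hdPS to control confounding | Not singled out |

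The one statement specific to the ICER says gross. The general statements can include the ICER, but none makes the adjusted version primary.

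**Illustrative size.** The article gives no mortality rate, cost or group share for its own population, so the following inputs are assumptions: exponential survival; control mortality h of 0.02, 0.04 or 0.06 per year; no true effect; confounding that acts like a mortality hazard ratio c of 0.80, 0.90 or 0.95 favouring the screened; and 20% or 50% screened. N = 90,000 and T = 5 years come from the article.

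- Life-years over 5 years: L(h) = (1 − exp(−5h))/h.
- Spurious difference: D = L(c·h) − L(h).
- Variance of restricted life-years: V(h) = 2[(1 − exp(−5h))/h² − 5·exp(−5h)/h] − L(h)².
- SE = √[V(c·h)/n₁ + V(h)/n₀].

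Example with h = 0.04, c = 0.90 and 50% screened:

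- L(0.04) = 0.18127/0.04 = 4.5317 and L(0.036) = 0.16473/0.036 = 4.5758, so D = 0.0441.
- V(0.04) = 1.367 and V(0.036) = 1.255, so SE = √[(1.367 + 1.255)/45,000] = 0.0076.
- D/SE = 5.8.

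| h per year | c | D (life-years) | SE, 50% / 20% screened | D/SE, 50% / 20% |
|---|---|---|---|---|
| 0.02 | 0.95 | 0.0117 | 0.0057 / 0.0071 | 2.0 / 1.6 |
| 0.02 | 0.90 | 0.0235 | 0.0057 / 0.0070 | 4.1 / 3.4 |
| 0.02 | 0.80 | 0.0471 | 0.0055 / 0.0067 | 8.5 / 7.0 |
| 0.04 | 0.95 | 0.0220 | 0.0077 / 0.0096 | 2.8 / 2.3 |
| 0.04 | 0.90 | 0.0441 | 0.0076 / 0.0094 | 5.8 / 4.7 |
| 0.04 | 0.80 | 0.0888 | 0.0075 / 0.0091 | 11.9 / 9.8 |
| 0.06 | 0.95 | 0.0309 | 0.0090 / 0.0112 | 3.4 / 2.8 |
| 0.06 | 0.90 | 0.0622 | 0.0089 / 0.0110 | 7.0 / 5.6 |
| 0.06 | 0.80 | 0.1256 | 0.0087 / 0.0107 | 14.4 / 11.8 |

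**Effect on the ratio.** Take a true hazard ratio of 0.95 and a confounding hazard ratio of 0.90. At h = 0.04 the true gain is 0.0220 life-years and the crude gain 0.0641. At the same incremental cost the crude ICER is 0.0220/0.0641 = 0.34 times the true one; h = 0.02 and h = 0.06 also give 0.34. This leaves out confounding of the cost difference, for which the article gives no figures.

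**The case against.** The strongest reply is that an ICER of screening against no screening is itself a comparison between the two groups. The general rule promises such comparisons with and without hdPS adjustment, and the abstract exempts nothing. A reader might infer from the primary-endpoint paragraph that the ICER will be unadjusted only, with adjustment reserved for the other comparisons. The documents do not say that, and the general statements can fairly be read to cover the ICER. This part of the reply stands. It does not remove the conflict: the general rule promises both versions and ranks neither, while the one specific sentence and the interval belong to the gross version.

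A second reply is that the method of adjusting costs and life-years belongs in a full analysis plan that is not shown. That is fair as to method. Which estimate is primary is different, because the article already fixes it, as gross.

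Two further inferences should not be drawn. One is that regression on the score cannot feed an ICER. It can: a cost regression gives an adjusted cost difference, and standardised predictions from a survival model give adjusted life-years. The other is that the planned bootstrap neglects the uncertainty of the estimated score. A gross ratio contains no score, and for an adjusted ratio the article does not say the score would be held fixed.

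Finally, the direction of bias is open. Frailer patients may be tested less, which would flatter screening; higher-risk patients may be tested more, which would do the opposite.

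**Conclusion.** The point holds as a conflict over which estimate is primary. The only ICER specified is gross and carries the only interval, in a comparison that the article itself describes as open to confounding and for which it relies on the hdPS. Followed literally, the headline result would be crude. It is not established that no adjusted ICER will be produced, nor that the reported result will be biased by any particular amount.

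Under the assumed ranges the spurious difference is about 0.01-0.13 life-years per person, or about 1.6 to 14 standard errors. Those figures rest on assumed mortality, strength and direction of confounding, and group shares. They show that modest confounding could exceed sampling error in a cohort of this size, and that a bootstrap of the crude ratio, which captures sampling error alone, would not reveal it. The choice of primary estimate should be settled before the analysis starts.

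**What to change.** In the primary-endpoint paragraph, state that the primary ICER is hdPS-adjusted in both its parts: the difference in mean 5-year cost and the difference in mean life-years over 5 years. Weighting, matching or regression standardisation would each serve; the plan should name one. State that the hdPS adjustment is repeated within each of the 5000 bootstrap replicates, so that the interval belongs to the adjusted ratio. Label the gross ICER as descriptive only, and bring the abstract, the general rule and this paragraph into line.

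The cost is a few sentences, more computing (the score is refitted in every replicate on about 90,000 patients) and possibly a somewhat wider interval. No new data are needed.

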### Recruitment of participants and follow‑up

The data will be extracted from January 1, 2008 to December 31, 2019. A selection period will be defined by the 7 years (January 1, 2008 to December 31, 2014) preceding the index date. It will enable us to identify eligible patients and measure all the variables needed for the calculation of the high dimension propensity score (hdPS). Each participant will be assigned to one of the two study groups on the index date (January 1, 2015), and then followed up to December 31, 2019 (Fig. 1).

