### Screening for silent CAD and risk of major cardiovascular events

Previous RCTs demonstrated no clinical benefit associated with routine CAD screening in asymptomatic T2DM patients, but population with a high cardiovascular burden and any organ vascular damage has not been investigated [11–14]. Also, the observed incidence of outcomes was much lower than expected in published RCTs evaluating the interest of routine CAD screening in individuals with T2DM (Table 1). The conduction of a new prospective RCT will be too expensive, time-consuming with difficulties for recruiting asymptomatic participants with a very high cardiovascular risk. Indeed, the DYNAMIT (Do You Need to Assess Myocardial Ischemia in Type-2 diabetes) study was stopped prematurely due to difficulties in recruitment of participants and a low incidence of cardiovascular events [12]. DYNAMIT included only one-fifth (631/3000) of the originally planned enrolment to detect a 20% relative risk reduction (RRR) in the primary endpoint (a composite of all-cause death, non-fatal myocardial infarction, non-fatal stroke, or heart failure requiring hospitalization or visit to emergency department) in people with T2DM at a high cardiovascular risk (aged 55 to 75 years with at least 2 other cardiovascular risk factors). A recent meta-analysis estimated that a large number of participants would be needed to demonstrate a potential benefit of the systematic CAD screening strategy to reduce the incidence of major cardiovascular events [15]. The optimal sample size for 20% RRR of major cardiac events should be 29,763 participants (19,548 for all-cause death). Therefore, a retrospective RWE study seems to be an appropriate approach to evaluate the long-term cost-effectiveness of systematic CAD screening strategy in T2DM subjects at a very high cardiovascular risk without known history of CAD. Of note, among 3.7 million people with diabetes in France, we estimate that at least 90,000 individuals will be eligible for our study in the SNDS database.

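### The primary bootstrap interval is placed on the cost-effectiveness ratio itself and becomes unreadable if the 5-year life-year difference is close to zero; no such case is provided for

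*Protocol article*

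**What the plan says.** The *Primary endpoint* section of the protocol article defines a ratio: "The incremental cost per life year saved over 5 years in CAD screening group" compared with no screening. The *Statistical analysis plan* section gives the estimate ("a gross estimate of the incremental cost per life-year gained at 5 years will be conducted") and then the interval: "The confidence interval (CI) of this incremental cost-effectiveness ratio will be estimated by boostrap (5000 iterations"). It does not name the type of bootstrap interval. It gives no rule for a life-year difference that is zero, negative or not distinguishable from zero.

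On the likely effect, the Discussion states: "Previous RCTs demonstrated no clinical benefit associated with routine CAD screening in asymptomatic T2DM patients". The same sentence goes on to say that patients with a high cardiovascular burden and organ damage, who are the target population here, were not studied. Table 1 lists four trials with hazard ratios of 0.80 to 1.00, and every confidence interval includes 1.

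On size: "Hence, we estimated that at least 90,000 patients would be eligible for our study".

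**The concern.** The ICER is the cost difference divided by the life-year difference, and it has no continuous meaning when the denominator passes through zero. A negative ratio can mean that screening is cheaper and better, or dearer and worse. A positive ratio can mean dearer and better, or cheaper and worse. When bootstrap life-year differences take both signs, sorting the ratios puts opposite conclusions next to each other and the same conclusion at opposite ends. The 2.5th and 97.5th percentiles of that list do not bound a range of plausible values for the cost of a life-year.

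In that case the primary result would be an interval from a large negative to a large positive sum, which could not tell a payer whether screening is worth its cost. The same replicates may nevertheless contain a clear answer.

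**Working it through.** **Inputs from the protocol article.** Sample size at least 90,000; follow-up of 5 years from 1 January 2015 ("and then followed up to December 31, 2019"); 5,000 bootstrap replicates; 5% error level, taken here as a two-sided 95% interval.

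**The plan's own figure.** 2,400,000 × 0.38 × 0.10 = 91,200, which agrees with the stated minimum of 90,000.

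**Assumptions that the documents do not give.** No-screening mortality of 3%, 4% or 5% per year with exponential survival; screened share of 50% or 25%; cost difference of EUR 500 or 1,000; cost SD of EUR 25,000; no correlation between cost and survival; percentile interval; EUR 30,000 per life-year as an illustrative threshold only.

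**Formulas.** For hazard λ, mean life-years over 5 years are RM = (1 − e^(−5λ))/λ, with variance V = 2[1 − e^(−5λ)(1 + 5λ)]/λ² − RM². The life-year difference is ΔLY = RM(screened) − RM(not screened), with SE = √(V₁/n₁ + V₀/n₀). The share of replicates at or below zero is Φ(−ΔLY/SE).

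**One case in full (4% per year, 45,000 per group, hazard ratio 0.98).**
- RM = 4.5405 and 4.5317, so ΔLY = 0.0088 years.
- SDs are 1.1598 and 1.1693, so SE = √((1.345 + 1.367)/45,000) = 0.0078.
- ΔLY/SE = 1.13, so 12.9% of replicates are at or below zero.
- SE of the cost difference = 25,000 × √(2/45,000) = EUR 167.
- Net benefit at EUR 30,000, with cost difference EUR 1,000: 30,000 × 0.0088 − 1,000 ≈ −736. Its SE is √((30,000 × 0.00776)² + 167²) ≈ 286. The interval is about EUR −1,298 to −175.

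**Across hazard ratios (4% per year, equal groups, cost difference EUR 1,000).** Ratio percentiles are from one million normal draws, because with 5,000 the extreme limits themselves move noticeably.

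| Mortality HR | ΔLY (years) | ΔLY/SE | Replicates ≤ 0 | ICER 95% percentiles (EUR) | Net benefit 95% interval (EUR) |
|---|---|---|---|---|---|
| 0.88 | 0.053 | 6.97 | 0% | 11,900 to 29,100 | 36 to 1,143 |
| 0.90 | 0.044 | 5.78 | 0% | 13,900 to 37,400 | −232 to 878 |
| 0.95 | 0.022 | 2.85 | 0.2% | 23,200 to 143,600 | −900 to 218 |
| 0.97 | 0.013 | 1.70 | 4.5% | −351,000 to 587,000 | −1,166 to −44 |
| 0.98 | 0.009 | 1.13 | 12.9% | −1.00 million to 1.14 million | −1,298 to −175 |
| 1.00 | 0 | 0 | 50% | −2.06 million to 2.02 million | −1,563 to −437 |
| 1.02 | −0.009 | −1.12 | 87% | −1.17 million to 1.01 million | −1,827 to −698 |

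The ratio intervals at 0.98 (screening prolongs life slightly) and 1.02 (shortens it slightly) are near mirror images and hardly tell the two apart. Net benefit does separate them, and both lie below zero at this threshold.

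**Range over the assumptions.** Replicates at or below zero: 3.0% to 9.9% at hazard ratio 0.97, 10.5% to 19.6% at 0.98, 50% at 1.00 in every case, and practically none at 0.90. With a cost difference of EUR 500 (4% per year, equal groups), net benefit at hazard ratio 1.00 is EUR −1,063 to 63, so it is not always decisive, but it can still be interpreted.

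**What Table 1 implies.** With SE(log HR) = (ln upper − ln lower)/3.92, the four trials have SEs of 0.370, 0.271, 0.253 and 0.394. Fixed-effect pooling gives 0.88 (0.65 to 1.19). This is a rough guide only, because the endpoints differ. The range covers both the region where the ratio interval works and the region where it fails.

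**The case against.** A reader might infer from the Discussion and Table 1 that the life-year difference will be near zero, so that failure is the most likely outcome. The documents do not support that. The four trials with hazard ratios had 26 to 62 events each. Wide intervals that include 1 show imprecision, not absence of effect. The endpoints are composites, and two of them count only cardiovascular death. The article itself says this risk group was not investigated. The pooled value of 0.88, if it held for mortality, would give a well-behaved ratio interval. The comparison is also non-randomised, so confounding could move the observed difference away from zero in either direction. All of this stands, and it limits the point to a conditional one.

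A small difference is also not the same as an indistinguishable one. At hazard ratio 0.95 the gain is only about 0.02 years, yet it is nearly three SEs from zero, and the ratio interval is wide but readable. This too stands.

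In simulation the percentile interval covers the true ratio 97-98% of the time at hazard ratios of 0.98 and 0.95, and 91% at 0.995. Formal coverage is therefore not the main failure. The limits are so extreme, and so mixed in meaning, that covering the true value conveys little. In the 4%, equal-group case, 20% of studies at hazard ratio 0.95 and 78% at 0.98 would have a life-year difference not distinguishable from zero. A proper confidence set for the ratio is then unbounded, and a finite interval hides this.

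The interval type is unstated, and the full plan may add a cost-effectiveness plane or acceptability curve. Their absence from an article is not the point. The point is that the stated primary inference rests on the ratio. Any interval read from the sorted ratios has the same ordering problem.

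Finally, a null result would not leave the study without any answer. The cost-consequence analysis, the separate analysis of all-cause death and the Cox models would still report. It is the primary endpoint that would be unreadable.

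**Conclusion.** The concern holds as a conditional one. The stated primary interval is sound if screening changes mortality by roughly 10% or more. It fails if the mortality hazard ratio is about 0.97 or nearer to 1. Between these it is wide, and at 0.95 still readable. These boundaries rest on 90,000 patients and on assumed mortality, allocation and costs that the documents do not give; the ranges above show that they move little within those assumptions. No prediction about the true effect is made or needed. A near-null survival difference lies within the range of the evidence that the article cites, and the primary analysis should be able to report it.

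**What to change.** Base the primary inference on the joint bootstrap distribution of the cost and life-year differences, from the same 5,000 replicates:

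- incremental net monetary benefit (threshold × life-year difference − cost difference) with a bootstrap 95% interval over a pre-set range of thresholds;
- the cost-effectiveness plane with the percentage of replicates in each quadrant;
- an acceptability curve over the same threshold range.

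Keep the ICER as a point summary. Give an interval for the ratio only under a numerical rule fixed in advance, for example that the 95% interval of the life-year difference excludes zero, and state the quadrant with it.

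The cost is a change of wording and no new computation. The real demand is that the threshold range be fixed before the analysis; the article gives none.
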